**Fig. 1 Fig1:**
[figure not shown]
Recruitment and follow-up flowchart

### Hypothesis and objectives

The study hypothesis is that “Prescription, Pedometer, Information, Logbook” intervention (PPIL) is better from Verbal Advice (VA) in increasing the physical activity of patients with cardiovascular risk factors.

The primary objective of the study is to determine whether PPIL is better from VA in increasing the weekly energy expenditure of participants at three months.

The key secondary objective is to determine whether PPIL is better from VA in increasing the weekly energy expenditure of participants at 12 months.

The other secondary objectives are to determine whether PPIL is better from VA in improving quality of life, reducing waist circumference, weight and arterial blood pressure, and to describe the deviations of doctors and patients from the recommended strategies.

### Primary and secondary outcomes

The primary outcome is the change at three months of the total weekly energy expenditure, measured by an accelerometer in Metabolic Equivalent Task-minute (MET-min), compared to baseline. The accelerometer (Actigraph wGT3x-BT validated in research [19–23]) is worn at the belt over a 7-day period, from morning to bedtime. The Swartz Adult Overground & Lifestyle algorithm [24] is used to convert from accelerometer counts to MET.

The key secondary outcome is the change at 12 months of the total weekly energy expenditure, measured by an accelerometer in MET-min, compared to baseline.

The other secondary outcomes are:Change at 3 and 12 months in the weekly time dedicated to moderate and high intensity physical activity, and in the weekly physical activity level in MET-min calculated by the International Physical Activity Questionnaire (IPAQ), from baseline.Change at 3 and 12 months in the scores on the SF36 quality of life questionnaire compared to baseline.Change at 3 and 12 months to weight, waist circumference and arterial blood pressure compared to baseline,Changes in the patient’s drug treatment at 3 and 12 months,Perceived obstacles to physical activity at 3 and 12 months as assessed by the Determinants of Physical Activity Questionnaire (DPAQ),Details of the physical exercise promotion strategies applied during the study,Compliance of patients with their doctor’s recommendations.

### Sample size

Studies by Kirk, et al. [25], Pinto, et al. [26], Baker, et al. [27] and Mutrie, et al. [28] were chosen as a base for sample sizing, considering their similarity to the PEPPER trial, their sample size and the outcomes reported. None of these studies reported measures in MET-min, but there is a linear relationship between the energy expenditure and the duration of physical activity, the step count or the raw accelerometer output: 15 min of moderate intensity physical exercise is equivalent to 45 MET-min.

Using a 2-tailed hypothesis, a sample of 140 patients in two groups of 70 will be necessary to detect a difference, between the two groups, of the change in total energy expenditure at three months of 105 MET-min/week (about 35 min of moderate intensity physical exercise per week), with an estimated standard deviation of 185 MET-min/week, an alpha risk of 5% and a power of 90%.

### Randomisation and blinding

Randomisation will occur at the first follow-up consultation after the first self-assessment period. Participants will be randomised to either the PPIL or the VA group by their GP. The group allocation will be achieved by a computerised dynamic randomisation using a minimisation algorithm based on nine criteria: diabetes (yes/no), body mass index (BMI) (< 30, ≥30), sex (female/male), hypertension (yes/no), employment status (employed/unemployed), hypercholesterolemia (yes/no), age (35-54y, 55-74y), education level (≤ A-level, > A-level) and follow-up doctor. The randomisation procedure will be concealed, centralised and performed by the Cellule de Méthodologie et Biostatistiques of Angers University Hospital.

The randomisation system will be internet-based with investigator access 24 h a day, seven days a week using a personal ID and PIN code.

Considering the nature of the interventions, it is not possible to blind investigators or patients.

### Data collection

Data from the study are collected during follow-up consultations and by self-assessment (questionnaires and accelerometer), with telephone reminders to patients and physicians in case the data are not received.

#### Socio-demographic data

The following data are collected at the beginning of the study: age, sex, education level, family unit (alone / with family), socio-professional category (1 - farmer, 2 -craftsman/trader/small employer, 3 - higher managerial and professional occupations, 4 - intermediate occupations, 5 - lower supervisory occupations, 6 - lower technical occupations, 7 - retired, 8 - other inactive), occupation rate (> 80%, ≤80%), employment type (physical / lightly physical / sedentary), living environment (urban, semi-urban, rural) and distance to workplace (≤5 km, between 5 and 10 km, > 10 km).

#### Risk factors and medical history

At inclusion, GPs will gather the following data: tobacco use, hypercholesterolemia, arterial hypertension, diabetes, significant medical history (cardiovascular, respiratory, orthopaedic, neurological diseases…) and drug history.

#### Energy expenditure and physical activity

Energy expenditure and physical activity will be measured at 0, 3 and 12 months, by two methods:Using an accelerometer (Actigraph wGT3x-BT), worn at the waist using an elastic belt during seven consecutive days, from morning to bedtime, to measure the total weekly energy expenditure in MET-min/week, the total time spent in moderate (between 3.75 and 7.49 MET-min) and high intensity (> 7.5 MET-min) physical activities; The default energy expenditure during the time when the accelerometer is not worn will be 1 MET-min.Using the self-administered International Physical Activity Questionnaire (IPAQ) [29], short version, covering the past seven days, to measure the weekly energy expenditure in MET-min/week.

#### Quality of life

Quality of life will be measured at 0, 3 and 12 months using the eight scores of the Short Form 36 (SF-36) self-administered questionnaire [30].

#### Clinical and morphological measures

GPs will assess the following data at 0, 3 and 12 months: systolic and diastolic arterial blood pressure, weight, height, waist circumference (National Institutes of Health method [31, 32]).

#### Change in health status and adverse events

Data are collected at 0, 3 and 12 months regarding changes in drug treatment (stable / increased / decreased), adverse events (acute serious pathological episode, new diagnostics of chronic or serious pathologies…) and, if available, the dates and values of the latest blood tests, including total cholesterol, HDL-C, LDL-C, triglycerides and HbA1c.

#### Perceived obstacles to change

Perceived obstacles to change will be assessed at 3 and 12 months using the self-administered Determinants of Physical Activity Questionnaire (DPAQ) [9].

#### Monitoring of patient compliance with and deviations from the protocol

The data collection plan includes the description of any deviation from the protocol in terms of physical exercise promotion strategy and the compliance of participants with their GP’s recommendations, in both the intervention and the control group. In particular, the following data will be collected in order to evaluate the study process:Compliance of GPs with the intervention (structured information given to patient, logbook given to patient, pedometer given to patient, content of the physical activity prescription…)Compliance of patients with the process: attendance to consultations, use of accelerometer, use of pedometer, percentage of logbook data filled...

### Data management and quality control

All data will be collected using an electronic Case Report Form (CRF), with all data stored centrally in Angers University Hospital. The data management team will be in charge of carrying out quality controls and monitoring of data modifications.

### Statistical analyses

A diagram will describe the participant selection process, with a descriptive analysis of their characteristics.

Quantitative variables will be expressed as mean ± standard deviation (median and inter-quartile interval if the normality hypothesis is not valid). Qualitative variables will be expressed as frequency and percentage.

Intention to treat analysis will be carried out, taking into account all randomised people. Multiple imputation techniques will be used to handle missing data.

An additional per-protocol analysis will also be carried out, taking into account those patients for whom the assessment criteria will be available.

The Student’s t-test (or the non-parametric Mann-Whitney U-test, depending on the variable distribution) and mixed models will be used to compare both groups for the primary outcome and for the other quantitative variables.

For qualitative variables, the Pearson’s chi-squared test (or the Fisher’s exact test, when necessary) will be used.

The level of significance is set to 0.05 and all tests are bilateral.

Bivariate analyses will be carried out for all outcomes. Additional multivariate analyses may be performed to adjust for significant factors. Backward stepwise regression techniques will be used to select confounders. Adjustment variables will include:

Sex (F/M),

Age (35-54y, 55-74y),

Education level (≤ A-level, > A-level),

BMI (< 30, ≥ 30),

Diabetes (yes/no),

Occupational rate (> 80%, ≤80%).

Living environment (urban, semi-urban, rural).

All hypotheses and tests are two-tailed.

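### The 3-month change is compared without adjusting for baseline energy expenditure, and the adjustment list omits it; a prespecified baseline-adjusted primary model would be more precise at no cost

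*Protocol article*

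**What the plan says.** Under Primary and secondary outcomes, the endpoint is a change score: "The primary outcome is the change at three months of the total weekly energy expenditure, measured by an accelerometer", relative to baseline. Under Energy expenditure and physical activity, "Energy expenditure and physical activity will be measured at 0, 3 and 12 months". Recruitment and follow-up, together with Randomisation and blinding, place the first 7-day recording before allocation, so the baseline value precedes treatment.

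Statistical analyses names two kinds of comparison for the primary outcome: Student's t-test (or Mann-Whitney) and mixed models. The abstract names mixed models only. Neither place says how baseline enters the mixed model.

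Adjustment comes afterwards and is discretionary: "Additional multivariate analyses may be performed to adjust for significant factors". Confounders are to be selected by backward stepwise regression. The listed variables are sex, age, education, BMI, diabetes, occupational rate and living environment. Baseline energy expenditure is not among them, nor is it one of the nine minimisation criteria.

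**The concern.** Baseline energy expenditure is the earlier measurement of the outcome itself, so it is an obvious candidate covariate, and the trial already collects it. The section goes into enough detail to name tests and list covariates, yet the t-test/Mann-Whitney comparison has no baseline term and the list leaves baseline out.

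A raw change score subtracts the whole baseline value. With equal variances at the two visits and a correlation below 1, the best linear adjustment subtracts only a fraction rho of it. The raw change therefore carries avoidable noise, and a chance baseline difference between arms pushes the estimate in the opposite direction. At stake is the width of the confidence interval for the primary and key secondary outcomes, and the margin left if some patients provide no accelerometer data.

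**Working it through.** **Inputs from Sample size.** The plan gives "a sample of 140 patients in two groups of 70", a difference "of the change in total energy expenditure at three months of 105 MET-min/week", and "with an estimated standard deviation of 185 MET-min/week, an alpha risk of 5% and a power of 90"%; the test is two-sided. The sentence concerns the change, so 185 is read as the SD of the change. The baseline-to-3-month correlation rho is not given and is varied from 0.3 to 0.9 as an assumption.

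**The plan's own figure.** The standardised difference is 105/185 = 0.568. The normal approximation gives 66 per arm (132 in total) for 90% power. The exact t-test gives 66.2, so 67 per arm (134). At 70 per arm, exact-t power is 91.5% (91.9% by the normal approximation). The stated design therefore meets its target without adjustment, with 6 patients (140 − 134, about 4%) to spare.

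**Variance with and without baseline.** Let s² be the variance at each visit, assumed equal.

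- Change score: 2s²(1 − rho)
- Baseline-adjusted: s²(1 − rho²)
- Ratio: (1 + rho)/2, so the adjusted SD is 185 × √((1 + rho)/2)

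For example, at rho 0.5 the adjusted SD is 185 × √0.75 = 160.2.

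| Assumed rho | Variance ratio | Adjusted SD | Power, 70 per arm | 95% CI half-width (MET-min/week) |
|---|---|---|---|---|
| unadjusted | 1 | 185 | 91.5% | 61.3 |
| 0.3 | 0.65 | 149.2 | 98.5% | 49.4 |
| 0.5 | 0.75 | 160.2 | 97.1% | 53.1 |
| 0.7 | 0.85 | 170.6 | 95.1% | 56.5 |
| 0.8 | 0.90 | 175.5 | 94.0% | 58.1 |
| 0.9 | 0.95 | 180.3 | 92.8% | 59.7 |

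Half-width is 1.96 × SD × √(2/70). Power is from the noncentral t; the single degree of freedom spent on baseline is ignored. A simulation of 4,000 trials at each of two rho values gave variance ratios of 0.77 (rho 0.5) and 0.84 (rho 0.7), against 0.75 and 0.85 by formula. Both estimators averaged close to the true 105.

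**Sensitivity to loss (assumed; the document gives no rate).** With 10% loss (63 per arm), unadjusted power is 88.5%; adjusted power runs from 97.5% at rho 0.3 to 90.0% at rho 0.9. With 20% loss (56 per arm), unadjusted power is 84.5%; adjusted power is 95.8%, 93.0%, 89.8%, 88.1% and 86.3% across the five rho values.

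**Chance imbalance.** Given an observed baseline difference D between arms, the change-score contrast is shifted by −(1 − rho)D. The standard error of D is s√(2/70), with s = 185/√(2(1 − rho)). At rho 0.5, s = 185, the standard error is 31.3, and a one-standard-error imbalance shifts the contrast by 0.5 × 31.3 = 15.6 MET-min/week, 15% of the target difference. At rho 0.7, s = 238.8, the standard error is 40.4 and the shift is 0.3 × 40.4 = 12.1.

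**The case against.** The strongest reply is that mixed models are named for the primary outcome, and alone in the abstract. A mixed model with energy expenditure at 0, 3 and 12 months as responses and a common baseline mean would recover the precision of ANCOVA. How baseline enters is detail that an article may leave to the full protocol or SAP. Defining the outcome as a change does not rule out adjustment either: regressing change on arm and baseline gives the same treatment estimate as regressing the 3-month value.

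This stands in part. It would be wrong to conclude that the plan certainly throws the baseline information away. But a mixed model on change scores, or an unconstrained group-by-time model with complete data, gives no gain, and the article does not say which form is meant. The t-test/Mann-Whitney comparison is unadjusted on any reading, and the covariate list is a stated choice rather than an omitted detail.

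A reader might also infer three stronger faults that the document does not support:

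- **Bias, or uncorrected regression to the mean.** Randomisation makes regression to the mean act equally on both arms in expectation, and the contrast is unbiased.
- **Baseline imbalance left uncorrected.** The change score subtracts baseline in full, so under the stated assumptions it over-corrects.
- **An underpowered trial.** Unadjusted power is 91.5% with full follow-up, above the stated 90%.

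It is also fair that the gain is small if repeat measurements correlate strongly: 5% of the variance at rho 0.9. That baseline is the strongest predictor of follow-up is a reasonable expectation, not something the document shows.

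**Conclusion.** The point holds as a free gain in efficiency. It is not an error of bias or a power shortfall. Under the plan's stated t-test/Mann-Whitney comparison, and possibly under its mixed model, the treatment effect is estimated with more variance than necessary. Baseline adjustment removes (1 − rho)/2 of that variance, from 35% at rho 0.3 to 5% at rho 0.9, and lifts power at 70 per arm from 91.5% to between 98.5% and 92.8%. These sizes rest on equal variances at baseline and 3 months, on 185 being the SD of the change, and on assumed correlations. For any rho below 1 the adjusted comparison is the more precise one, apart from the negligible cost of estimating one coefficient.

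**What to change.** Name one baseline-adjusted model as the primary analysis. Two forms serve:

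- ANCOVA of the 3-month value (or the change) on arm and baseline energy expenditure; or
- the planned mixed model over 0, 3 and 12 months, with baseline means constrained equal between arms.

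Prespecify baseline as a fixed term outside the backward stepwise selection. Apply the same approach to the 12-month key secondary outcome and to the other continuous outcomes with a baseline value. Report the adjusted mean difference with its 95% CI; the t-test or Mann-Whitney comparison can remain as a supporting analysis.

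The cost is wording only. The baseline recording is already in the schedule, so no extra data, visits or patients are needed.

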### Strengths and limitations of this study

This is a multi-centre, open, randomised controlled study design. Considering that the interventions are different in nature, there is no possible blinding in the intervention or in the collection of anthropometric data.We considered it was impractical and too difficult to ensure to ensure that randomized patients do not meet each other or share information about the study. Therefore there is a possibility that some patients included in the study and assigned to different groups knew each other and were able to share details about the study. It is also possible that some patients included in the control group (verbal advice) decided on their own to use a pedometer that influenced their physical activity.The physical activity of patients is assessed objectively (primary outcome) using accelerometers and questionnaires instead of questionnaires alone. However there is a possibility that the fact of wearing the accelerometer had an impact on the physical activity of the patient. It is also possible that some patient did not wear the accelerometer appropriately because they found it cumbersome.The intervention studied was designed to ensure minimal deviation from usual patient follow-up, in order to make the intervention easier to apply, to limit the workload of GPs, and to limit the financial cost of additional consultations.The simple intervention requires limited resources, including limited staff, financial input and time, and limited changes to usual practice.Considering the small recruitment size, the intervention effect on health outcomes, such as control of hypertension, control of glycaemia, or improvement in dyslipidaemia, is beyond the study statistical power. Therefore the primary outcomes of the study are only surrogate outcomes. However the available literature gives us confidence that increased physical activity as measured in this study will probably lead to improved health outcomes.Considering the risk of withdrawal at 1 year and the relatively small sample size, primary outcomes are considered at 3 months rather than at 1 year.

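### The optional adjusted analysis picks covariates by backward stepwise selection from a list holding only five of the nine minimisation factors, so no comparison, as described, is matched to the allocation

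*Protocol article*

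**What the plan says.** The protocol article, section Randomisation and blinding, assigns treatment by "dynamic randomisation using a minimisation algorithm based on nine criteria". The nine are diabetes, BMI, sex, hypertension, employment status, hypercholesterolaemia, age, education level and follow-up doctor.

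The section Statistical analyses compares the groups on the primary outcome by t-test (or Mann-Whitney) and by mixed models; the abstract names mixed models only. The random effects are not given. The section then adds: "Additional multivariate analyses may be performed to adjust for significant factors". The next sentence reads: "Backward stepwise regression techniques will be used to select confounders". The adjustment variables listed are sex, age, education level, BMI, diabetes, occupational rate and living environment.

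**The concern.** Minimisation makes the arms more alike on the chosen factors than simple randomisation would. Where those factors predict the outcome, the true sampling variation of the treatment difference shrinks. An analysis that leaves them out does not register this and reports a standard error that is too large.

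The stepwise rule raises a separate problem. Baseline differences in a randomised trial arise by chance, so there are no confounders to discover by significance testing. Adjustment serves precision and agreement with the allocation, and both call for terms fixed in advance. Backward selection can also drop the five minimised factors that are on the list. The text is unclear as well: one sentence treats the variables as candidates for selection, the next as variables that will be included, and the whole analysis is optional. In an open trial, that leaves room to choose the adjusted estimate after the results are known.

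**Working it through.** **1. The two lists side by side.**

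| Variable | Minimised | In adjustment list |
|---|---|---|
| Sex, age, education level, BMI, diabetes | yes | yes |
| Hypertension | yes | no |
| Hypercholesterolaemia | yes | no |
| Employment status | yes | no |
| Follow-up doctor | yes | no |
| Occupational rate | no | yes |
| Living environment | no | yes |

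The overlap is 5 of 9. Occupational rate (above 80% or not) is a different variable from employed/unemployed, so it does not fill that gap.

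**2. The plan's own figure.** The section Sample size gives a difference in "the change in total energy expenditure at three months of 105 MET-min/week", "with an estimated standard deviation of 185 MET-min/week, an alpha risk of 5% and a power of 90"%, and 70 patients per arm, two-tailed.

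- n per arm = 2 × (1.960 + 1.282)² × 185² / 105² = 65.2, so 66 (67 by the exact t-test).
- At 70 per arm, SE = 185 × √(2/70) = 31.3 and 105 / 31.3 = 3.36. Power is Φ(3.36 − 1.96) = 91.9% (91.5% by noncentral t).

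The stated 90% is reached with a little to spare. This calculation uses no covariates.

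**3. Size of the mismatch.** The article gives neither the variance explained by the factors (R²) nor the intraclass correlation (ICC) by doctor, so both are assumed. The simulation used 140 patients, 15 GPs, minimisation with an 0.8 biased coin, eight binary factors of equal prevalence and effect, and SD 185. The stepwise model started from the seven listed variables and removed those with p > 0.05. The nine-factor model carried doctor as a fixed effect. There were 1,500 replicates for (a), 3,000 each for (b) and (c), and 1,000 for each power figure. SE ratio means the average model SE divided by the true SD of the estimate, with no treatment effect.

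| Scenario | Quantity | t-test | Stepwise list | All nine |
|---|---|---|---|---|
| (a) ICC 0, R² 0 | SE ratio | 0.99 | 0.98 | 0.99 |
| | Type I error | 5.7% | 5.7% | 5.9% |
| (b) ICC 0.05, R² 0.10 | SE ratio | 1.05 | 1.02 | 1.00 |
| | Type I error | 3.5% | 4.3% | 4.4% |
| | Power at 105 | 92.5% | 93.7% | 93.6% |
| (c) ICC 0.10, R² 0.20 | SE ratio | 1.15 | 1.08 | 1.01 |
| | Type I error | 2.4% | 3.5% | 4.7% |
| | Power at 105 | 94.0% | 95.3% | 96.7% |

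Monte Carlo standard errors are √(0.05 × 0.95 / 1,500) = 0.6 points in (a), √(0.05 × 0.95 / 3,000) = 0.4 points for type I error in (b) and (c), and about √(0.94 × 0.06 / 1,000) = 0.8 points for power. The 5.7% in (a) is therefore compatible with 5%.

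**4. Plausibility check.** With perfect balance, the unadjusted SE would be too large by a factor of 1/√(1 − total explained share). That is 1/√0.85 = 1.085 in (b) and 1/√0.70 = 1.195 in (c). The simulated 1.05 and 1.15 lie below these ceilings, as they should with imperfect balance.

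**5. If the doctor is in the model.** With the seven listed variables plus doctor, the SE ratio was 1.02 in (b) and 1.05 in (c), with type I error 4.1% in both. A doctor effect would thus remove part of the excess in (c) and none visible in (b).

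**The case against.** Several stronger readings are tempting, and the article does not support them.

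- *That stepwise selection drives the primary comparison.* It does not clearly do so. It stands under an additional analysis that may or may not be run; the primary comparison is by t-test or Mann-Whitney and mixed models.
- *That the doctor is left out of every model.* The random effects are unstated, and a condensed article may leave them to the full plan. The covariate list shows only that doctor is not among the listed adjustment variables.
- *That the standard errors are wrong.* This holds only if the minimisation factors predict change in energy expenditure, and nothing in the article shows that they do. Scenario (a) shows no material error.
- *That false positives rise.* The omission errs on the conservative side. Stepwise selection gave the same type I error as the plain t-test in (a), so no inflation was detectable.
- *That the listed adjustment costs as much as no adjustment.* With five of nine factors available, the SE excess is 2 to 8%, against 5 to 15% for the t-test. In (b), power with the stepwise list and with all nine factors is the same within simulation error.

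Nor is it a good argument that occupational rate has no obvious value for retired patients: employment status coded employed/unemployed has the same difficulty.

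What remains is stated text rather than missing detail: a selection rule and a named list, both poorly suited to a trial minimised on nine factors.

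**Conclusion.** The point holds in a limited form. The factor mismatch and the data-dependent selection are certain from the text. The effect on inference is conditional: nil if the minimisation factors are not prognostic, and otherwise conservative. In the two prognostic scenarios, type I error is 2.4 to 4.3% across the t-test and the stepwise list. The power forgone against the nine-factor model is about 1 to 3 points for the t-test and 0 to 1.4 points for the stepwise list. Power stays above the planned 90% in both, so no new sample size follows.

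These sizes rest on the assumed ICC, R², biased-coin probability and factor prevalences. Mann-Whitney was not simulated, and no gain from adjusting for the baseline value is counted. The simulation also assumes that the treatment effect does not vary between doctors. If it did, a standard error ignoring doctor could be too small for inference beyond these doctors.

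**What to change.** Delete the stepwise sentence or confine it to exploratory work. For the primary and key secondary outcomes, pre-specify one mixed model with these terms:

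- the baseline value of the outcome, as a fixed term;
- the eight patient-level minimisation factors, as fixed terms coded as in the algorithm;
- follow-up doctor, as a random effect.

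Move occupational rate and living environment to exploratory analysis.

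The cost is wording, since the algorithm already needs every minimisation factor, plus about nine degrees of freedom of 140 (eight binary factors and one baseline value). Fitting doctor as a fixed effect would add 15 − 1 = 14, assuming one GP per practice, for about 23 in all.

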### Participants

Participants are recruited by their general practitioner (GP) in 15 GP practices in the Pays-De-La-Loire region.

Participants are 35 to 74-year-old adults, consulting their usual general practitioner (GP) for a non-urgent matter, and followed-up every three months for hypertension, hypercholesterolemia or non-insulin dependent type 2 diabetes. Patients will be judged insufficiently active by their general practitioner on the basis of at least their answers to two questions:“Do you practice any sports, including cycling, an hour or more every week?”“Does your work involve physical activities?”

The inclusion criterion is fulfilled by a negative answer to both questions.

Exclusion criteria are: having a health condition that contraindicates a moderate physical activity, as judged by the general practitioner; being unable to walk without human or material help; having any health condition, including psychiatric or cognitive impairments, that would prevent the participant from fully understanding the study and his or her doctor’s advice, as judged by the general practitioner; being unable to communicate in French, or refusing to participate.

Patients will be able to withdraw their consent or request to leave the study at any time and regardless of the reason.

The investigator can discontinue, temporarily or permanently, the participation of a patient in the study for any reason that would be in the best interest of the patient, especially in case of serious adverse events.

The exclusion of a patient is required in case of:Withdrawal of consent for participation,Serious event with consequences for the patient’s ability to follow the study protocol.

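### The optional adjusted analyses code age and BMI in two classes although numeric values can be had: a small, avoidable loss of precision

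*Protocol article*

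**What the plan says.** All places are in the protocol article.

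- **Statistical analyses.** The adjusted models are supplementary and optional: "Additional multivariate analyses may be performed to adjust for significant factors". Covariates are then chosen by a data-driven procedure: "Backward stepwise regression techniques will be used to select confounders". Age stands in the candidate list as "Age (35-54y, 55-74y", and BMI is split at 30.
- **Randomisation and blinding.** The minimisation factors use the same cuts: "age (35-54y, 55-74y" and "body mass index (BMI) (< 30, ≥30".
- **Socio-demographic data.** "The following data are collected at the beginning of the study: age, sex, education level". Age carries no classes here, whereas occupation rate, living environment and distance to workplace are given with theirs.
- **Clinical and morphological measures.** At 0, 3 and 12 months the GPs record "systolic and diastolic arterial blood pressure, weight, height, waist circumference", so BMI can be calculated as a number.
- **Participants.** "Participants are 35 to 74-year-old adults", so each age class spans 20 years.

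**The concern.** A minimisation algorithm needs classes, but a regression does not. Carrying the allocation classes into the model treats a 36-year-old and a 54-year-old as alike, and likewise a BMI of 20 and one of 29.9. Three things follow if the outcome varies smoothly with age or BMI:

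- the two-class term explains less outcome variance than the number would, so the adjusted treatment estimate is less precise;
- chance differences between arms within a class are neither balanced by the minimisation nor adjusted by the model;
- the weaker term is more likely to be removed by backward selection, and then the covariate contributes nothing.

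At stake is some precision in the adjusted comparisons of energy expenditure, quality of life, weight, waist circumference and blood pressure.

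**Working it through.** **1. The plan's own figure.** Inputs from Sample size: difference 105 and SD 185 MET-min/week, two-sided alpha 5%, power 90%, 70 per group.

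n per group = 2 × (1.960 + 1.282)² × (185/105)² = 65.2, rounded up to 66, or 132 in total. With 70 per group, power is 91.9% (91.5% from the t distribution). The stated 140 is adequate and slightly conservative. No covariate enters this calculation.

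**2. Share of explained variance kept by a two-class split.** With a linear effect, this share is the squared correlation between the covariate and its split.

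- Age spread evenly over 35 up to 75, cut at 55: total variance 40²/12 = 133.3. The class means are 45 and 65, so the between-class variance is 100. Share kept = 100/133.3 = 0.75.
- Normal variable cut z SDs from its mean: share kept = φ(z)² / [Φ(z)(1 − Φ(z))]. At z = 0 this is 0.1592/0.25 = 0.637. At z = 0.5 it is 0.1240/0.2133 = 0.581.

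The loss is therefore 25% to 42% for cuts at or near the centre.

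**3. Other assumed distributions.** The article gives none, so the following are illustrations (2,000,000 draws each before truncation).

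| Covariate and cut | Assumed distribution | Loss |
|---|---|---|
| Age at 55 | normal 55, SD 10, truncated to the eligible range | 32% |
| Age at 55 | normal 60, SD 10, truncated | 35% |
| Age at 55 | normal 62, SD 8, truncated | 46% |
| Age at 55 | normal 65, SD 8, truncated | 56% |
| BMI at 30 | normal 30, SD 5 | 36% |
| BMI at 30 | normal 28, SD 5 | 40% |
| BMI at 30 | normal 27, SD 4 | 48% |

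**4. Residual variance.** Let R² be the share of outcome variance explained by numeric age and BMI together (assumed), and k the share kept after the split. The ratio of residual variances, classes to numbers, is (1 − kR²)/(1 − R²).

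| R² | k = 0.75 | k = 0.581 |
|---|---|---|
| 5% | 0.9625/0.95 = 1.013 | 0.9710/0.95 = 1.022 |
| 10% | 0.925/0.90 = 1.028 | 0.9419/0.90 = 1.047 |
| 15% | 0.8875/0.85 = 1.044 | 0.9129/0.85 = 1.074 |

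Multiplied by 140, the excess is worth 2-3 patients at 5% and 4-10 patients at 10-15%.

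**5. Power for the primary difference**, 70 per group, SD = 185 × √(1 − kR²).

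| R² | Numeric terms | 25% loss | 40% loss | 55% loss |
|---|---|---|---|---|
| 2% | 92.4% | 92.3% | 92.2% | 92.1% |
| 5% | 93.1% | 92.8% | 92.6% | 92.5% |
| 10% | 94.3% | 93.7% | 93.4% | 93.0% |
| 20% | 96.4% | 95.4% | 94.7% | 94.1% |

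At R² = 20% the difference is 1.6 points at 40% loss and 1.7 at 42% (SD = 185 × √0.884 = 173.9, power 94.6%). In the off-centre case of 55% loss it reaches 2.3 points.

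**6. Within-class imbalance.** Its contribution to the treatment difference has mean zero and SD 185 × √(R² × loss) × √(2/70). This is 2.2 MET-min/week at R² = 2% with 25% loss, and 8.8 at R² = 20% with 40% loss. The unadjusted standard error is 185 × √(2/70) = 31.3.

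**7. Backward selection.** Assume one covariate that explains 5% as a number and 3% after a 40% loss, and a retention level of 0.05. The expected test statistic is √(140 × 0.05/0.95) = 2.71 as a number and √(140 × 0.03/0.97) = 2.08 as classes. The chance of retention is about Φ(2.71 − 1.96) = 77% against Φ(2.08 − 1.96) = 55%. If the covariate is dropped altogether, the residual variance is 1/0.95 = 1.053 times what it could have been.

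**The case against.** The case for leaving the text alone has real force.

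- **Optional models.** The adjusted analyses may not be run, and selection may drop either variable. The comparison named for the primary outcome is a t-test or Mann-Whitney test together with mixed models, and the two-class coding is not tied to it. A reader might infer that age and BMI are bound to enter the primary model in this form. The text does not say so, and the calculations in steps 4 and 5 apply only where both terms are in the model. This stands.
- **No bias.** A reader might infer that uncorrected imbalance within classes distorts the estimate. Allocation is randomised with minimisation on these classes, so such imbalance has no expected direction and is already part of the standard error. This stands.
- **Conditional figures.** A reader might take a fixed percentage of information as lost. The article reports no distribution of age or BMI and no relation to any outcome, so every percentage depends on the linear effect and on where the cut falls. This stands.
- **A recognised choice.** Adjusting for minimisation factors in the form used for allocation is defensible, and a straight line is itself an assumption. If an outcome really changed in a step at the cut, the classes would fit better. This stands in part: a step exactly at 55 years or at a BMI of 30 is less plausible than a gradual change, and linearity can be checked.

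Collection of age in years is inferred from the absence of classes and is not stated outright.

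**Conclusion.** The point holds as a minor gain in precision for supplementary analyses. The article itself fixes the two-class coding, and numeric values should be to hand. Under a roughly linear effect the split gives up about 25-42% of what each covariate could explain for near-central cuts, and up to about 55% for off-centre ones. In practical terms that is 1-2% more residual variance if the two covariates explain 5% of the outcome variance, and 3-7% more at 10-15%. The power difference is about 1.7 points at 20% with a near-central cut, or 2.3 points at 55% loss. The retention calculation adds that two-class terms are more likely to be lost in backward selection, under an assumed retention level of 0.05.

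The distributions and the shares explained are all assumptions. The documents do not support reading this as a flaw in the primary comparison, a source of bias or a defect of the sample size.

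**What to change.** Keep the two classes of age and BMI for the minimisation only. In the covariate list under Statistical analyses, replace them with age in years and baseline BMI in kg/m², each as a continuous linear term. State in advance that linearity will be checked and that a simple spline will be used if it fails.

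The cost is an edit to two list items. Linear terms use the same number of parameters as the classes, and a spline adds a few. No new data are needed, provided age is recorded in years as the data collection section implies. The drawback is that a functional form must be chosen for each variable and applied across outcomes that may not behave alike.
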